## Abstract

**Background:**

Pulmonary rehabilitation programs have been shown to increase functional exercise capacity and quality of life in COPD patients. However, following the completion of pulmonary rehabilitation the benefits begin to decline unless the program is of longer duration or ongoing maintenance exercise is followed. Therefore, the aim of this study is to determine if supervised, weekly, hospital-based exercise compared to home exercise will maintain the benefits gained from an eight-week pulmonary rehabilitation program in COPD subjects to twelve months.

**Methods:**

Following completion of an eight-week pulmonary rehabilitation program, COPD subjects will be recruited and randomised (using concealed allocation in numbered envelopes) into either the maintenance exercise group (supervised, weekly, hospital-based exercise) or the control group (unsupervised home exercise) and followed for twelve months. Measurements will be taken at baseline (post an eight-week pulmonary rehabilitation program), three, six and twelve months. The exercise measurements will include two six-minute walk tests, two incremental shuttle walk tests, and two endurance shuttle walk tests. Oxygen saturation, heart rate and dyspnoea will be monitored during all these tests. Quality of life will be measured using the St George's Respiratory Questionnaire and the Hospital Anxiety and Depression Scale. Participants will be excluded if they require supplemental oxygen or have neurological or musculoskeletal co-morbidities that will prevent them from exercising independently.

**Discussion:**

Pulmonary rehabilitation plays an important part in the management of COPD and the results from this study will help determine if supervised, weekly, hospital-based exercise can successfully maintain functional exercise capacity and quality of life following an eight-week pulmonary rehabilitation program in COPD subjects in Australia.

## Background

Chronic Obstructive Pulmonary Disease (COPD) is the fourth leading cause of death in Australian males, the sixth leading cause of death in females [1] and resulted in 5000 deaths in 2003 [2]. COPD is a progressive, disabling disease, which has a significant impact on the health care system [1,3]. Early diagnosis and management of COPD is a priority of health care services throughout Australia. Management of COPD involves optimising medical therapy, commencing smoking cessation and participating in pulmonary rehabilitation.

Pulmonary Rehabilitation is a multi-disciplinary approach to the management of patients with respiratory disease. The program is individually tailored to the needs of the patient, combining exercise, self-management education and psychosocial support [4]. Pulmonary rehabilitation has been shown to improve functional exercise capacity, quality of life and dyspnoea, and to reduce hospital admissions and length of stay [5].

Following pulmonary rehabilitation, benefits in terms of functional exercise capacity and quality of life are maintained for up to nine months [6-8]. However, the benefits appear to decline by twelve months [9] unless the program is of longer duration [10] or involves ongoing maintenance exercise [11,12]. There is little evidence to support the best method of maintaining these gains long-term and the above studies differ in length and intensity of the exercise programs. As the majority of pulmonary rehabilitation programs in Australia are of eight weeks duration, it is important to determine the best method of maintaining functional exercise capacity and quality of life, twelve months following an eight-week pulmonary rehabilitation program.

The aim of the study is to determine if supervised, weekly exercise following an eight-week pulmonary rehabilitation program will maintain the benefits to twelve months.

## Methods

### Participants

This study will be a prospective, randomised controlled trial in participants diagnosed with COPD. Participants will be recruited consecutively on completion of an eight-week pulmonary rehabilitation program and randomised into either a maintenance exercise group (ME) or a control group and followed for 12 months. Randomisation will be by computerised random number generation in concealed envelopes prepared by an investigator not involved in subject testing or training. The chief investigator will conduct both testing and training so will be aware of group allocation.

Participants will be excluded if they have experienced an exacerbation of COPD in the previous month, if they require supplemental oxygen, or if they have co-morbidities such as severe cardiovascular, neurological or musculoskeletal conditions that will prevent them performing functional exercise tests. The flow of participants through the study will reflect the recommendations from the Consolidated Standards of Reporting Trials (CONSORT) statement [13], and is illustrated in Figure 1. Participants will receive written and verbal information explaining the study and written consent will be obtained from all subjects. Ethics approval to conduct the study has been obtained from the Ethics Committee of Sydney South West Area Health Service (Eastern Zone). The study will take place at Royal Prince Alfred Hospital (RPAH), Sydney, Australia.

**Figure 1 F1:**
[figure not shown]
**Flow of participants through the study**. PRP = pulmonary rehabilitation program; COPD = chronic obstructive pulmonary disease; x/wk = times per week.

### Interventions

Participants randomised to the ME group will attend hospital-based pulmonary rehabilitation once a week for supervised exercise training and will also be asked to follow an unsupervised home exercise program on four other days a week. The hospital-based program will be individually designed and supervised by a qualified physiotherapist and will consist of lower limb and upper limb exercise (Table 1) similar to those that the subject performed during the eight-week pulmonary rehabilitation program. More specifically, the program will consist of a) lower limb endurance training in which the participant will perform 20 minutes of stationary cycling and 20 minutes of walking, b) lower limb strength training using weight machines for the quadriceps and gluteal muscles, c) upper limb endurance training which will consist of arm cycle ergometry and unsupported arm exercises with light weights [14], d) upper limb strength training using weight machines for the latissimus dorsi and pectoralis major/minor muscles. All strength-training exercises will be performed in three sets of ten repetitions.

**Table 1 T1:** Components of the exercise programs

	**Supervised**	**Unsupervised**
**Equipment**	Yes	No
**Intensity**	Dyspnoea 3–4 Borg Scale	Dyspnoea 3–4 Borg Scale
**Duration**	20 mins W 20 mins SC 30 mins AC, LWM, AWM, UAE	30 mins W 30 mins S, Sq, S/S, UAE
**Total duration**	70 mins	60 mins
**Frequency** (per wk)	1	4 (ME group) 5 (Control group)
**Venue**	Hospital gym	Home

AC = arm crank ergometer; AWM = arm weight machine; LWM = leg weight machine; ME = maintenance exercise; mins = minutes; SC = stationary cycle; S = step-ups; Sq = wall squats; S/S = sit to stand exercises; UAE = upper limb unsupported arm exercises as described by Ries [14]; W = walking.

Participants randomised to the control group will follow standard care and be asked to follow an unsupervised home exercise program on five days per week which will consist of 30 minutes of walking, unsupported arm exercises [14] and lower limb strengthening exercises five days per week (Table 1). The exercises will be explained and illustrated in the home exercise booklet that all participants will have received during pulmonary rehabilitation. Participants in the ME group will be asked to follow the same home exercise program four days a week. Participants in the control group will not be contacted between testing sessions. Participants in both the ME and control groups will be asked to complete an exercise diary by ticking boxes to indicate the exercises they complete.

### Outcomes measures

All outcome measures will be recorded at baseline, three, six and 12 months post pulmonary rehabilitation (Figure 2). The outcome measures are outlined below.

**Figure 2 F2:**
[figure not shown]
**Timeline for recruitment and measurement**. Rehab = eight week pulmonary rehabilitation program; ME = maintenance exercise.

1. Functional exercise capacity will be measured by:

a) Six-minute walk test (6MWT) [15]. This test measures the distance a participant is able to walk in six minutes and will be performed using a protocol standardised for factors known to affect results e.g. instructions, encouragement, number of tests and type of track [15]. Participants will be asked to walk as far as they can in six minutes, to do the best they can, and to cover as much ground as possible. Every minute participants will be made aware of the time and will be given standardised encouragement e.g. "You are doing well – you have 5 minutes to go!" This will be alternated each minute with "Keep up the good work – you have 4 minutes remaining!" If participants need to stop they can do so, but will be asked every 15 seconds to commence walking again when they feel able.

b) Incremental shuttle walk test (ISWT) [8]. This test is an incremental, progressive, symptom-limited test. The participants will listen to instructions from an audio-tape [8]. They will be asked to walk along a ten-metre track turning around two cones in time with beeps from the tape and to continue until they indicate they need to stop or are unable to keep pace with the beeps. The total distance walked will be recorded.

c) Endurance shuttle walk test (ESWT) [16]. This test is similar to the ISWT in terms of track length and instructions from an audiotape, however, as it is a measure of endurance the participant will be asked to walk at a constant speed for as long as possible (maximum of 20 minutes) following a two minute warm up period. The speed for the ESWT for each participant will be based on the result of his/her ISWT, using the recommended equation [16]. The distance walked during the test will be recorded.

Before and immediately after each walk test the following measurements will be recorded a) oxygen saturation and heart rate using a portable saturation monitor (RAD-5v Masimo Corp, Irvine, CA, USA); b) dyspnoea using the Borg Scale category ratio 0–10 scale [17]. The 6MWT, ISWT and ESWT will be performed twice at each time point to account for a learning effect [18]. Participants will rest for at least 30 minutes between tests or until oxygen saturation, dyspnoea and heart rate return to resting levels. The better distance walked in each test will be recorded for analysis. Testing will be completed over a two-day period at each time point.

2. Quality of life will be measured by:

a) St George's Respiratory Questionnaire (SGRQ) [19]. This is a disease specific, questionnaire shown to be sensitive to changes following pulmonary rehabilitation [19,20]. The SGRQ is a self-administered questionnaire consisting of 50 items. It will be scored from 0 – 100 with zero indicating the best health and 100 the worst. The questionnaire will be explained to the participants. They will be asked to complete it to the best of their ability and to ask for help if they have difficulty understanding the questions.

b) Hospital Anxiety and Depression Scale (HADS) [21]. The HADS has been found to be a reliable instrument for detecting states of depression and anxiety in hospital medical outpatient clinics [21].

3. Lung function will be measured by:

a) Spirometry. This will be performed in accordance with American Thoracic Society standards [22]. Forced expiratory volume in one second (FEV_1_) and forced vital capacity (FVC) will be measured using a mass flow sensor (Sensormedics Vmax 20 Pulmonary Spirometry Instrument; Sensormedics Corporation, Yorba Linda, California, USA). The spirometer will be calibrated immediately before each test using a three litre-calibrating syringe. The highest value for FEV_1 _and FVC after three reproducible trials will be recorded and compared to predicted normal values [23].

b) Lung Volumes. These will be performed in accordance with American Thoracic Society standards [24] using a body plethysmograph (Sensormedics V6200 Autobox Body Plethysmograph; Sensormedics Corporation, Yorba Linda, California, USA). The plethysmograph pressure transducer and the mouth pressure transducer will be calibrated by an automatic internal 50 ml calibration syringe prior to testing. Total lung capacity (TLC) will be determined by summating the best inspiratory capacity (IC) with the mean functional residual capacity (FRC) from three acceptable tests. Residual volume (RV) will be determined by subtracting the best vital capacity (VC) from the calculated TLC value [25]. Results will be compared to predicted normal values for lung volumes [26].

### Statistical analysis

For all outcome measures, the mean difference between the ME group and the control group in the change from baseline to 12 months will be determined and the significance of these mean differences will be tested by repeated measures ANOVA. Significance will be set at p < 0.05. Intention to treat analysis will be used.

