### Power calculation

The sample size calculation is based on functional walking capacity as this is the major outcome of the study. Redelmeier and colleagues [27] have reported that in COPD participants, following pulmonary rehabilitation, the minimal clinically important difference is 54 metres. Using this value as the difference in walking distance to be detected between the two groups and taking an effect size of 0.7, it was estimated that the sample size required to achieve an 80% power for a 2-sided test at 5% alpha would be 32 subjects per group. To allow for 15% attrition, 38 subjects will be recruited in each group.

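### The plan targets the 12-month change but does not name the repeated measures ANOVA term that tests it, and the usual four-visit terms test something else

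*Protocol article*

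**What the plan says.** The Statistical analysis section of the protocol fixes the quantity of interest for every outcome: "the mean difference between the ME group and the control group in the change from baseline to 12 months will be determined". It then names the method: "the significance of these mean differences will be tested by repeated measures ANOVA". The threshold follows: "Significance will be set at p < 0.05". No model term, contrast or set of visits is given.

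The Outcomes measures section sets four occasions: "All outcome measures will be recorded at baseline, three, six and 12 months post pulmonary rehabilitation".

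The Power calculation section sizes the trial for one two-group difference in walking distance. It cites a report that "the minimal clinically important difference is 54 metres", proceeds by "taking an effect size of 0.7", and concludes that "the sample size required to achieve an 80% power for a 2-sided test at 5% alpha would be 32 subjects per group". The Background and Discussion sections also put the question at twelve months.

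**The concern.** Repeated measures ANOVA on two groups and four visits yields two standard between-group tests. The group-by-time interaction, on 3 df, asks whether the group difference varies across visits in any way. The group main effect averages the difference over all visits, including baseline, where randomised groups should not differ. Neither is the difference in change from baseline to 12 months.

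If either supplies the p-value, the test and the reported estimate answer different questions. An early difference that has gone by 12 months could yield a significant result for a trial whose question is whether benefit lasts to 12 months. The stated 80% power, set for a single difference, would not describe that test. With no deciding term named, the choice could also be made after the data are seen.

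A 12-month contrast taken inside the classical four-visit ANOVA targets the right quantity, but its standard error uses an error term pooled over all visits. That is valid only under sphericity. If correlation falls as visits lie further apart, the pooled error is too small for the longest interval, which is the one of interest.

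**Working it through.** **Inputs from the protocol.** Difference 54 m, effect size 0.7, 32 per group, two-sided 5%, 80% power, visits at 0, 3, 6 and 12 months.

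**Assumptions, not in the protocol.** The implied standard deviation, 54/0.7 = 77.14 m, is taken as that of the 12-month change. Visit profiles and within-patient correlations are illustrative.

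**1. The plan's own figure.** n = 2(1.960 + 0.842)²/0.7² = 32.04 per group, so 32 is reproduced (33 if rounded up). At n = 32 the expected test statistic is 0.7 × √(32/2) = 2.8. Power is 79.96% by the normal approximation and 78.7% by the t-test. The sample size is therefore that of a 1-df comparison.

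**2. Group-by-time F, equal correlations.** The error variance is 77.14²/2 = 2,975.5. With δ the group difference at each visit, the noncentrality is λ = (32/2) × Σ(δ − mean δ)² / 2,975.5, on 3 and 186 df.

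| Difference at 0, 3, 6, 12 months (m) | Σ(δ − mean)² | λ | F significant |
|---|---|---|---|
| 0, 27, 27, 0 | 729 | 3.92 | 34–35% |
| 0, 54, 0, 0 | 2,187 | 11.76 | 82% |
| 0, 54, 54, 0 | 2,916 | 15.68 | 92% |
| 0, 13.5, 27, 54 | 1,594.7 | 8.57 | 68% |
| 0, 18, 36, 54 | 1,620 | 8.71 | 69% |
| 0, 0, 0, 54 | 2,187 | 11.76 | 82% |

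The first three rows have no difference at 12 months. Simulation agrees: 34% for the first row, 82–83% for the second, 92–93% for the third. In simulated profiles with no 12-month difference, the 12-month comparison rejects in 4–6% of runs whatever happens at months 3 and 6. With a true 54 m its power is 78–80%.

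**3. Group main effect.** For profiles reaching 54 m at 12 months, simulated power is 6–46%, with correlation 0.7 or 0.9.

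**4. ANOVA on baseline and 12 months only.** Its interaction F equals the squared t-statistic on the change scores (0.8371 for both in a check on simulated data). Here test and target coincide.

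**5. 12-month contrast with the four-visit pooled error.** Suppose correlation decays by a factor of 0.98 per month.
- Correlations at 3, 6, 9 and 12 months apart are 0.941, 0.886, 0.834 and 0.785.
- The mean over the six visit pairs is (2 × 0.941 + 2 × 0.886 + 0.834 + 0.785)/6 = 0.879.
- In units of the single-visit variance, the pooled error implies a variance of change of 2(1 − 0.8788) = 0.242. The true value for baseline to 12 months is 2(1 − 0.7847) = 0.431.
- The ratio is 0.563, so the critical value 1.96 acts as 1.96 × √0.563 = 1.47. Type I error is then about 14%, which simulation confirms.
- A t-test on the 12-month change itself keeps 5%. The uncorrected 3-df F rejects in about 7% of null trials.

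**The case against.** A reader might infer that the plan adopts an omnibus four-visit test as its decision rule. The protocol does not say so. It ties the test to the 12-month differences, and the visit schedule says when outcomes are recorded, not which visits enter the model. On a two-visit reading there is no mismatch, and the stated power describes the test. This stands, so the point is conditional on how the ANOVA is run.

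The article is also condensed, and a fuller plan may name the contrast or a sphericity correction. That limits the weight of the point. But the article does fix both a target and a method, and the method's usual output on the recorded data does not test the target. Nor do the usual sphericity corrections, which adjust the degrees of freedom of the F, repair the pooled standard error of a single contrast.

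Finally, the profiles with only an early effect are not the most likely ones. The Background says that after rehabilitation "benefits in terms of functional exercise capacity and quality of life are maintained for up to nine months", which suggests late separation. There the omnibus test loses no power (82% against 79%), and a false signal from early visits is less likely. This is fair as to likelihood. It does not change what the F test means, and a profile that diverges steadily still costs about 11 points of power.

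**Conclusion.** The point holds as an unresolved ambiguity with a real consequence. The protocol names a 12-month target and a method whose usual four-visit tests do not address it, and it does not say which term decides. Of the readings examined, only the ANOVA restricted to baseline and 12 months both tests the stated quantity and keeps its error rate without assuming sphericity.

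If the omnibus F decides, rejection with no 12-month difference runs from about 34% to 92% over the early-only profiles tabulated. Power under linear divergence is 68% rather than 79%. If a contrast with pooled error decides, type I error could be near 14% under the assumed decay. These sizes rest on 32 per arm and the assumed profiles and correlations. The figures in metres also rest on reading 77 m as the standard deviation of change. They are illustrations, not forecasts.

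The documents do not support saying that the trial is undersized. The 32 per group is reproduced for the 1-df comparison.

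**What to change.** State in the Statistical analysis section that the decisive test for each outcome is the 1-df contrast, ME minus control, in change from baseline to 12 months, reported with its 95% CI. Take it from a model with group-by-visit terms and an unstructured covariance. Alternatively, use a two-group test based on the variance of the 12-month change itself; with complete data the two give the same estimate. Present months 3 and 6 as supportive estimates, and say that neither the overall group-by-time F nor the group main effect decides the result.

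The cost is one or two sentences, with no new patients, visits or measurements. The sample size then matches the test. The one thing given up is a little power if the groups separate only late (79% against 82% under the assumptions above). If this contrast is what the investigators already intend, saying so costs nothing.

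### Free improvement: adjusting the 12-month comparison for each outcome's own baseline would be more precise than the unadjusted difference in change that the plan specifies

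*Protocol article*

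**What the plan says.** The Statistical analysis section of the protocol article sets a single analysis that applies to every outcome. On the effect to be estimated it states: "the mean difference between the ME group and the control group in the change from baseline to 12 months will be determined". The method of testing that it names is repeated measures ANOVA. No covariate is named there or elsewhere in the article.

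The baseline values are available. The Outcomes measures section states: "All outcome measures will be recorded at baseline, three, six and 12 months post pulmonary rehabilitation". The abstract places baseline after the eight-week programme, so it marks the start of the randomised period.

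The Power calculation section rests on walking: "The sample size calculation is based on functional walking capacity as this is the major outcome of the study". It takes a difference of 54 m ("the minimal clinically important difference is 54 metres") and reaches the sample size by "taking an effect size of 0.7". The result is that "the sample size required to achieve an 80% power for a 2-sided test at 5% alpha would be 32 subjects per group", which an allowance of 15% for attrition raises to 38 recruited per group. It does not say whether 0.7 is standardised by the SD of the change or by the SD at one time point, and it gives no correlation between baseline and 12 months.

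**The concern.** A change score subtracts the whole baseline value, which fixes the slope of the 12-month value on baseline at 1. With equal variances at the two times the true slope is r, which is below 1, so the change score over-corrects for any chance difference between the arms at baseline. ANCOVA estimates the slope instead, and so has a smaller variance.

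Naming repeated measures ANOVA does not by itself recover this. With baseline as one of the repeated levels, the group-by-time contrast from baseline to 12 months is still the unadjusted difference in change. A baseline covariate, or a model that holds the baseline means equal, would recover the efficiency. The article states neither.

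At stake is the width of the interval for the 12-month comparison in a trial planned to about 80% power with 32 analysed per group.

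**Working it through.** **Inputs from the Power calculation section.** Difference 54 m; effect size 0.7; two-sided 5%; power 80%; 32 per group analysed; 38 per group recruited. Implied SD = 54/0.7 = 77.1 m.

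**Inputs assumed.** The correlation r between baseline and 12 months, which the article does not give, over the range 0.3 to 0.9; equal variances at the two times.

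**Step 1: the plan's own figure.** Normal approximation: n = 2(1.960+0.842)²/0.7² = 32.04, so 32 gives 79.96% power and strict rounding up gives 33. With the noncentral t (noncentrality 0.7×√(32/2) = 2.80, 62 df), power at 32 per group is 78.7% and 34 per group are needed for 80%. Attrition: 32/0.85 = 37.6, so 38. The stated 32 and 38 reproduce within rounding and choice of formula.

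**Step 2: relative variance.** With common variance s² at both times:

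- change score: variance proportional to 2s²(1−r)
- ANCOVA: variance proportional to s²(1−r²)
- ratio: (1−r²)/(2(1−r)) = (1+r)/2

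**Step 3: power if 0.7 is standardised by the SD of change.** The effective effect size under ANCOVA is 0.7/√((1+r)/2). Noncentral t, 32 per group, 61 df for ANCOVA:

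| r | Variance ratio | Variance saving | Change score | ANCOVA |
|---|---|---|---|---|
| 0.5 | 0.75 | 25% | 78.7% | 88.9% |
| 0.7 | 0.85 | 15% | 78.7% | 84.8% |
| 0.8 | 0.90 | 10% | 78.7% | 82.8% |
| 0.9 | 0.95 | 5% | 78.7% | 80.7% |

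Charging ANCOVA for the estimated slope as well lowers the first three figures to about 88.4%, 84.2% and 82.1%, so the gain survives at this sample size. A simulation (4000 trials per setting, 32 per group) gave, for change score and ANCOVA, 79.1% and 88.3% at r=0.5, 78.6% and 82.5% at r=0.8, and 77.7% and 79.3% at r=0.9.

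**Step 4: power if 0.7 is standardised by the SD at one time.** The effect size is 0.7/√(2(1−r)) for the change score and 0.7/√(1−r²) for ANCOVA:

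| r | Change score | ANCOVA |
|---|---|---|
| 0.3 | 64.4% | 82.3% |
| 0.5 | 78.7% | 88.9% |
| 0.7 | 94.5% | 97.1% |
| 0.8 | 99.2% | 99.6% |

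**Step 5: effect of a chance baseline imbalance.** With 77.1 m as the SD of change, the single-time SD is s = 77.1/√(2(1−r)). One standard error of the baseline difference at 38 per group is s√(2/38), and the change-score estimate shifts by (1−r) times that. This simplifies to 77.1×√((1−r)/38):

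- r=0.5: 8.8 m
- r=0.8: 5.6 m
- r=0.9: 4.0 m

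The target difference is 54 m.

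**The case against.** The strongest reply is that this is a preference for efficiency and not an error. That stands. In a randomised trial the difference in change is unbiased over randomisation and keeps its type I error, and if 0.7 refers to the SD of change the trial has about its planned power without adjustment.

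A second reply is that the size of the gain depends on a correlation that the article does not give. That also stands. At r=0.9 the gain is about two points, and if 0.7 refers to the single-time SD it is under three points at r=0.7 and under half a point at r=0.8.

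A third is that the powers compare a two-sample test on change with ANCOVA at one visit, whereas the plan names repeated measures ANOVA over four visits. The figures therefore illustrate relative precision for the 12-month contrast; they are not the power of the planned model.

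A fourth is that a condensed article may leave covariates to a fuller document. This carries less weight. The article does not leave the effect measure open: it fixes the difference in change for all outcomes and names the test.

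A reader might go further and infer that chance baseline differences will be material because walk distances are noisy and no stratification is described. The article does not support this. It standardises the six-minute walk test, repeats every walk test and analyses the better distance, and it gives no reliability figure. Its silence on stratification is only silence. A one-standard-error imbalance moves the estimate by 4 to 9 m. That shift is also the same loss of precision seen conditionally on the observed baseline, and not a second defect.

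**Conclusion.** The point holds as a free improvement. The stated analysis is valid, but for any r below 1 with equal variances it is less precise than one adjusted for baseline values that the trial already collects. The variance saving is 25% at r=0.5 and falls to 5% at r=0.9. In power at 32 per group, that is about ten points at r=0.5 under either meaning of the effect size and about two points at r=0.9 if 0.7 uses the SD of change. The largest gain in the range examined, about 18 points, arises at r=0.3 if 0.7 uses the single-time SD. All of these sizes rest on an assumed r.

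It would be wrong to conclude that the 12-month comparison is biased, that the trial is shown to be underpowered, or that a fixed share of participants could be saved. The algebra is certain; the practical gain is not known from the article.

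**What to change.** Change the one sentence in the Statistical analysis section. For each continuous outcome, estimate the 12-month difference between the groups adjusted for that outcome's own baseline value. Use either ANCOVA or a repeated-measures model of the three-, six- and 12-month values with baseline as covariate, reading off the group contrast at 12 months. Report raw mean changes by group descriptively.

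The cost is wording only: no extra visit, test or participant, and no change to the sample size. Making the change before outcome data are seen also removes any later choice between adjusted and unadjusted results.

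### Repeated measures ANOVA, as classically run, analyses complete cases only and so does not by itself deliver the stated intention-to-treat analysis at 15% attrition

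*Protocol article*

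**What the plan says.** The Statistical analysis section defines the target for every outcome as the difference between the ME and control groups in change from baseline to 12 months, and says that "the significance of these mean differences will be tested by repeated measures ANOVA". It then adds: "Intention to treat analysis will be used". It gives no exclusion rule for missed visits.

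The Outcomes measures section fixes four occasions: "All outcome measures will be recorded at baseline, three, six and 12 months post pulmonary rehabilitation". The Power calculation section expects loss: "To allow for 15% attrition, 38 subjects will be recruited in each group". The Interventions section makes contact differ by arm. The ME group attends hospital once a week, whereas "Participants in the control group will not be contacted between testing sessions".

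**The concern.** Classical repeated measures ANOVA needs a complete row of data for each participant. Unless missing values are filled in first, a participant without a 12-month value is deleted, and their 3- and 6-month measurements are deleted too. If all four occasions enter the model, a participant who attends at 12 months but missed an earlier visit is deleted as well.

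The plan thus names a method which, in its standard form, analyses completers, next to a commitment to intention to treat. The trial asks whether benefits decline over a year, and each assessment involves repeated walk tests spread over two days. Participants who deteriorate may be the least able to attend. If so, deleting them bears directly on the primary estimate.

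**Working it through.** **1. The plan's own sample size.** Inputs from the Power calculation section: "the minimal clinically important difference is 54 metres", "taking an effect size of 0.7", and 80% power at two-sided 5%.

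- Normal approximation: n = 2 × (1.96 + 0.8416)² / 0.7² = 32.04 per group. That is 33 if rounded up; the stated 32 gives 79.96% power.
- Attrition: 32 / (1 − 0.15) = 37.6, so 38. The stated figure reproduces.
- Implied SD: 54 / 0.7 = 77.1 m. The article does not say which SD this is; below it is taken as the SD of the change.

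**2. Who leaves a complete-case analysis at 15% loss.**

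- Per group: 38 × 0.85 = 32.3 remain.
- Overall: 76 × 0.15 = 11.4, so about 11 to 12 of 76 leave.
- Power at 32.3 per group, effect size 0.7: 80.3% (normal) or 79.1% (noncentral t). The inflation does its job.

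**3. Power if intermittent missed visits are added.** The documents give no rate for these. Assume that 5% or 10% independently miss each of months 3 and 6, and that all four occasions enter the ANOVA.

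| Missed at each of months 3 and 6 | Complete cases per group | Power, normal | Power, t |
|---|---|---|---|
| 0% | 38 × 0.85 = 32.3 | 80.3% | 79.1% |
| 5% | 38 × 0.85 × 0.95² = 29.2 | 76.2% | 74.8% |
| 10% | 38 × 0.85 × 0.90² = 26.2 | 71.6% | 70.0% |

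On one scale (t), the cost is about 4 to 9 points.

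**4. Bias if loss depends on decline.** All of the following are assumptions: 20% of controls leave after month 6; their log-odds of leaving rise by b per SD of worse 6-month change; ME loss is unrelated to outcome; the 6- and 12-month changes correlate at r. Let m be the mean standardised 6-month change among control completers, obtained by integrating over a normal distribution with the intercept set to give 20% loss. Controls who stay look better than all controls by r × 77.1 × m, so the complete-case estimate is 54 − r × 77.1 × m.

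| b | m | r = 0.5 | r = 0.75 |
|---|---|---|---|
| 0.5 | 0.096 | 54 − 3.7 = 50.3 m | 54 − 5.6 = 48.4 m |
| 1 | 0.173 | 54 − 6.7 = 47.3 m | 54 − 10.0 = 44.0 m |
| 2 | 0.262 | 54 − 10.1 = 43.9 m | 54 − 15.1 = 38.9 m |

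The range is about 39 to 50 m. Weaker dependence gives less: at b = 0.25 and r = 0.5 the bias is about 2 m. If the same loss fell on the ME arm instead, the sign would reverse, giving 54 + 3.7 to 54 + 15.1, or about 58 to 69 m. An analysis that uses the 6-month value recovers 54 m in this example, but only because loss was assumed to depend on that observed value.

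**The case against.** The strongest reply has four parts.

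- **Intention to treat can mean analysis as allocated.** On that meaning it is compatible with repeated measures ANOVA, and imputing first or fitting the repeated-measures model by likelihood would also reconcile the two statements. This stands. A reader might infer that the paragraph contradicts itself, but the article states no exclusion of participants with missed visits, so a contradiction is not shown.
- **Missing-data rules are commonly left to a full protocol or SAP, which is not at hand.** This stands for the detail. It does not dispose of the point, which concerns the method actually named rather than an absent rule.
- **The only contrast named is baseline to 12 months.** If just those two occasions enter the ANOVA, a missed 3- or 6-month visit removes nobody. This stands, so the extra power loss is conditional. Participants without a 12-month value are still deleted and their interim data go unused.
- **The loss patterns are assumed.** This stands. A reader might infer from the contact rules that controls will be lost more often. Weekly hospital attendance for a year could equally raise ME loss, and the article gives no arm-specific rate.

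**Conclusion.** The concern holds in a limited form. The named method, as classically run without imputation, is a complete-case analysis. At the plan's own 15% attrition it would leave out about 11 to 12 of 76 randomised participants, so it does not by itself deliver an analysis of everyone randomised.

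It would be tempting to add that the trial becomes underpowered. The documents do not support that: the only loss they state is already covered by recruiting 38 per group. Power of about 75% to 70% arises only with the assumed intermittent misses and the four-occasion reading.

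Bias matters more than power. The 39 to 50 m range against a true 54 m rests on the assumed mechanism in step 4 of the working and shows what is possible, not what is predicted. The direction is unknown. This is a should-fix point.

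**What to change.** In the Statistical analysis section, replace repeated measures ANOVA with a likelihood-based linear mixed model for repeated measures. It should:

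- include all randomised participants as allocated and every observed visit;
- have group-by-visit terms, with baseline either constrained equal across arms or used as a covariate (the constrained form also keeps participants who have a baseline but no follow-up value);
- give the 12-month between-group difference in change as the primary estimate, which is the contrast the plan already defines.

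Add one sensitivity analysis that departs from missing at random, for example a delta adjustment applied to participants who drop out. Settle this before outcome data are seen.

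The cost is analysis wording and slightly more analysis work, with no new patients or measurements. The downside is that the primary result then relies on missing at random, which the data cannot verify; the sensitivity analysis is there for that reason.
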